**Common Intervention to both treatment groups: Education and advice**

All subjects will receive verbal and written advice and education on lumbar spinal stenosis based on a patient information publication on spinal stenosis written by the American College of Rheumatology(32) emphasising the benefits of remaining active. (There are currently no guidelines or 'standard care' relating to conservative treatment for NC or LSS or directed at older patients with degenerative spinal conditions, but European Guidelines for the management of chronic non-specific low back pain with or without referred leg pain recommend brief educational interventions among other recommended treatments.)

**Physiotherapy exercise programme**

Each patient randomised to this group will be taught a programme of exercises by the treating physiotherapist, selected from a list of possible exercises (see below)and will be instructed to perform the selected programme of exercises twice daily. These exercises are based on flexion movements and postural adaptation to reduce symptoms from neural compression and include exercises improve fitness. The treating physiotherapist will review each subject at least 4 times and up to six times during the 6 week treatment period and will guide each subject in progressing the exercises (intensity, duration or repetitions) as appropriate. The physiotherapist will encourage compliance during treatment and encourage continuation of the exercise programme after the treatment period. In order to standardise the physiotherapy rehabilitation programme, a training session for physiotherapists administering interventions will be held by the study co-ordinator prior to commencement of the study.

*Follow-up*

All outcome measures will be repeated at 8 weeks and questionnaire outcomes will be repeated at 12 months from randomisation. These measures will be administered by the study co-ordinator who will be blinded to the intervention received.

All clinical assessment and treatment sessions will be administered in primary care outpatient clinics most convenient to the study participants.

*Dropouts and anticipated problems with compliance*

Problems with compliance and participant dropout from the trial are expected to be minimal due to the nature of the interventions and relatively short trial period. For genuine dropouts, every effort will be made to retrieve exit data for the primary endpoint, which may include telephone follow-up. The intention-to-treat approach to the analysis of this pragmatic trial designs ensures that compliance failures in both treatment arms will contribute valid data to the evaluation.

*Statistical Analysis*

The Academic Unit employs a statistician who has input into preparation of this application and who will work with the study team during the analysis phase. Descriptive exploration will compare the pre and post intervention data for the two groups, exploring for change in Swiss Spinal Stenosis (SSS) symptom severity and physical function scores. Inferential analysis of the pre-and post-intervention SSS symptom severity data will be based on multi-variable models appropriate to the data type, including baseline data as covariates (ANCOVA). The primary analysis will be undertaken according to intention to treat principles, with missing data excluded. A secondary analysis will also be performed where missing data will be analysed assuming worst-case values.

*Study timetable*

The study will have a 3 month run-in period, and will allow 18 months for recruitment.

Following 12 month follow-up, a further 3 months will be allowed for data cleansing, analysis, and preparation of the final report by the end of the three year trial period.

*Trial Management*

A trial steering committee, with an independent chair and lay representation will be set-up within the Leeds Academic Unit of Musculoskeletal Disease. The trial steering committee will receive 3-monthly reports from the study co-ordinator regarding recruitment and trial progress and will be responsible for external reporting to the funder and regulatory authorities. This committee, in conjunction with the Academic Unit's standing data-monitoring committee (chaired by [name]) will monitor adverse event management and all data-related aspects of the management of the trial. Day to day trial management will be overseen by a trial management group comprising the grant holders, the department's business manager and trial staff.

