**Trial procedure**

This is a single blind pragmatic randomised controlled trial. Both the intervention group and the control group will receive educational information and advice. Subjects randomised to receive the active physiotherapy intervention in addition to advice will be taught a rehabilitation programme tailored to address the posture-related pain and dysfunction associated with neurogenic claudication.

*Outcome Measurement*

Primary outcome measures will consist of score changes in the symptom severity scale of the Swiss Spinal Stenosis (SSS) questionnaire to be measured at 8 week follow-up assessment. The SSS has been been used since the early 1990s, and was specifically designed for the evaluation of patients with symptoms associated with lumbar spinal stenosis. It has been shown to be a reliable and valid outcome measure for this patient group(26).

Secondary outcome measures will include the Oswestry Disability Index (a commonly used measure of pain and function in low back pain), the General Well-being Index (providing a quality of life measure), objective measurement of walking tolerance (shuttle walking test), and 12 month Swiss Spinal Stenosis score.

*Sample size*

This study will be powered to detect a 0.5 point difference in the primary outcome measure; the Swiss Spinal Stenosis questionnaire symptom severity scale: The Minimum Clinically Important Difference for scores in this measure has been determined previously as a change of at least 0.5 points in the symptom severity scale and in the physical function scale (27). Population standard deviations of samples reported in previous studies (28,29) range from 0.48 to 0.56; and the more conservative figure of 0.56 has been adopted for powering this study.

The proposed sample size is based on the ability to detect a difference (Δ) in treatment groups of 0.5 points in the symptom severity scale, with a standard deviation of 0.56, and based on a power of 90% (alpha 5%). The required sample size at exit is 28 subjects and 28 controls. To allow for group size differences due to randomisation, and for a drop-out rate of 20%, a total recruitment of 76 patients is planned.

*Subject Recruitment*

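### Exercise-arm patients share physiotherapists who choose and progress their treatment, but neither the sample size nor the named ANCOVA allows for this, so the confidence interval may be too narrow if therapists differ

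*Protocol*

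**What the plan says.** Under Physiotherapy exercise programme, each patient allocated to exercise "will be taught a programme of exercises by the treating physiotherapist, selected from a list of possible exercises". Over the six-week treatment period the same therapist sees the patient at least four and up to six times and "will guide each subject in progressing the exercises (intensity, duration or repetitions) as appropriate". Treatment takes place in several primary care clinics, chosen for the participants' convenience.

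Variation in delivery is limited in two ways. Before the study starts, "a training session for physiotherapists administering interventions will be held by the study co-ordinator". The Exercise programme section also gives a written menu, with at least one exercise to be prescribed from each of five sections. The control arm receives standardised advice at the first physiotherapy appointment, and no course of reviews is described for it.

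The Sample size paragraph rests on the "ability to detect a difference (Δ) in treatment groups of 0.5 points in the symptom severity scale", with an SD of 0.56, 90% power and 5% alpha. It concludes that "The required sample size at exit is 28 subjects and 28 controls". The further allowance is for unequal group sizes and "for a drop-out rate of 20%, a total recruitment of 76 patients is planned".

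Statistical Analysis names "multi-variable models appropriate to the data type, including baseline data as covariates (ANCOVA", and mentions no therapist or clinic term. The number of physiotherapists is not given; the protocol uses only the plural.

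**The concern.** Patients treated by the same physiotherapist share that therapist's choice of exercises, pace of progression and encouragement to comply. Their outcomes may therefore be correlated, mainly in the exercise arm. An ordinary ANCOVA takes residuals as independent. If therapists differ in effect, its standard error for the treatment difference is too small, its interval too narrow, and its false-positive rate above the nominal 5%.

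The protocol itself treats variation between therapists as something to control, since the training session is there to standardise delivery. No statistical provision accompanies it. One part cannot be repaired later: if the therapist's identity is not captured as patients are treated, no subsequent analysis plan can examine the question.

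**Working it through.** **Inputs from the protocol (Sample size):** difference 0.5, SD 0.56, power 90%, alpha 5% (sidedness not stated), 28 per arm at exit, 20% drop-out, 76 recruited.

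**Assumed, because the protocol does not give them:** k = 2, 4 or 8 therapists with equal caseloads; ICC ρ = 0.01, 0.05 or 0.10; no clustering in the control arm.

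**Step 1: the plan's own figure.** Normal approximation, two-sided: n = 2 × [0.56 × (1.960 + 1.282) / 0.5]² = 26.4, so 27 per arm. The exact t calculation gives 89.6% power at 27 and 90.7% at 28, so 28 per arm reproduces. One-sided alpha gives 22 and does not. No design effect is contained in the figure. For drop-out, 56 / 0.8 = 70, so 76 leaves six spare for unequal groups.

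**Step 2: clustering in one arm.** With m = 28/k patients per therapist, the exercise-arm design effect is DE = 1 + (m − 1)ρ. The variance of the difference is multiplied by f = (1 + DE)/2, and the true SE is √f times the SE that ignores clustering. Approximately:

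- actual alpha = 2 × [1 − Φ(1.96/√f)]
- power = Φ(0.5 / (0.1497 × √f) − 1.96), where 0.1497 = 0.56 × √(2/28)

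Example, k = 4 and ρ = 0.05: m = 7, DE = 1.30, f = 1.15, √f = 1.072. Alpha = 2 × [1 − Φ(1.828)] = 6.8%. Power = Φ(3.115 − 1.96) = 87.6%.

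| Therapists | ICC | SE ratio | Actual alpha | Power at 28 per arm |
|---|---|---|---|---|
| 2 | 0.01 | 1.03 | 5.8% | 89.9% |
| 2 | 0.05 | 1.15 | 8.9% | 82.7% |
| 2 | 0.10 | 1.29 | 12.7% | 73.9% |
| 4 | 0.01 | 1.02 | 5.3% | 90.9% |
| 4 | 0.05 | 1.07 | 6.8% | 87.6% |
| 4 | 0.10 | 1.14 | 8.6% | 83.4% |
| 8 | 0.01 | 1.01 | 5.1% | 91.3% |
| 8 | 0.05 | 1.03 | 5.7% | 90.0% |
| 8 | 0.10 | 1.06 | 6.5% | 88.3% |

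Without clustering, power on this approximation is 91.6%.

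**Step 3: what offsets the power loss.** Recruiting 76 with 20% drop-out leaves 76 × 0.8 / 2 = 30.4 per arm. At ICC 0.05, power is then 84.9%, 89.7% and 92.0% for 2, 4 and 8 therapists. Baseline adjustment can add more. With an assumed baseline correlation of 0.5, the residual SD is 0.56 × √0.75 = 0.485. Applying the ICC to that residual, four therapists at ICC 0.10 give SE = 0.485 × √(2/28) × 1.140 = 0.148, and power Φ(0.5/0.148 − 1.96), about 92% (91% by the t distribution). Two therapists at ICC 0.10 still give only about 85% at 28 per arm. Neither offset changes the SE ratio or the actual alpha in the table, apart from a slight rise in both when m grows from 28/k to 30.4/k.

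**Step 4: what a therapist model can detect.** With four therapists of seven patients, the ratio of between- to within-therapist mean squares is distributed as λ × F(3, 24), where λ = (1 + 6ρ)/(1 − ρ). The variance estimate is zero or negative when F < 1/λ. For ρ = 0.02, 0.05 and 0.10, λ = 1.143, 1.368 and 1.778, and the probability is 53%, 46% and 36%.

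**The case against.** The strongest objection is that this faults silence. The analysis paragraph calls for models suited to the data type and does not say that patients are treated as independent. A therapist term is the kind of detail that an analysis plan may add, and that plan is not shown. This stands against any claim that the protocol rules out a therapist term. It does not reach the sample size, which the protocol fixes without a design effect, or the recording of the therapist, which has to be settled before treatment starts.

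The training session and the menu would tend to lower the ICC. Tailoring exercises to the patient is part of the intervention in a pragmatic trial and does not by itself create correlation within therapists. That is fair, and it makes a low ICC plausible, but nothing in the protocol shows that the ICC is zero.

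A reader might go further and infer four things that the protocol does not support:

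- **That only a few physiotherapists treat.** No number is given, the service is city-wide, and the size of the effect depends heavily on this number.
- **That the interval is certainly too narrow.** This requires an ICC above zero.
- **That true power is below 90%.** Step 3 shows that the margin and baseline adjustment can restore it in many of the cases considered.
- **That an effect due to one therapist would go unseen.** No case report form is shown, so it cannot be said that the therapist goes unrecorded.

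**Conclusion.** The point holds in conditional form. The nesting is stated, the sample size makes no allowance for it, and the named ANCOVA contains no therapist term. If therapists differ in effect and the analysis is run as named, precision is overstated.

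The size rests on assumed therapist numbers and ICCs, equal caseloads and an unclustered control arm. With eight or more therapists, or an ICC near 0.01, the effect is small. It becomes material with two to four therapists and an ICC of 0.05 or more, where a nominal 5% test runs at roughly 7% to 13%. A fall in power below 90% is possible but not shown. This is an inexpensive improvement to the plan, not a flaw that invalidates it.

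**What to change.** 1. Record the treating physiotherapist for each exercise-arm patient, and report the number of therapists and of patients per therapist.
2. Keep the ANCOVA as the primary analysis.
3. Pre-specify a supporting, partially nested version of the same model, with a therapist random intercept in the exercise arm only and small-sample degrees of freedom. Report its interval beside the primary one.
4. State the rule in advance: if the supporting interval includes zero and the primary one does not, the report says that the result is sensitive to therapist clustering.

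The cost is one field on the case report form and one extra model. The drawbacks are a somewhat wider supporting interval and an imprecise therapist variance. Because the variance estimate can often be zero even when clustering is present (Step 4), agreement between the two models must not be reported as proof that there is none.

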**Advice and Information**

**Verbal education and advice**

Standardised verbal education and advice will be provided for all study participants at their first physiotherapy clinic appointment. This information will include:

- Description of Neurogenic claudication symptoms

- Description of spinal stenosis and the pathological process causing symtpoms

- Explanation of the diagnosis, based predominantly on medical history

- Brief explanation of the causes of stenosis, predominantly degenerative changes in the

lumbar spine

- Explanation of how and why posture affects the symptoms of neurogenic claudication

**- Discussion of the available treatments for lumbar spinal stenosis, including**

**physiotherapy, spinal injection, surgery.**

**- Discussion around the benefits of exercise, and improving/maintaining fitness**

**Written education and advice**

**A written information and advice leaflet will be given to all study participants on their first physiotherapy clinic appointment. This leaflet is based on information from the American College of Rheumatology patient information website.**

**Exercise programme**

*The following exercise programme is aimed at addressing the specific dysfunctions associated with neurogenic claudication and is based on exercises advocated in current available literature and research in this area.*

*Your physiotherapist should prescribe at least one exercise selected from each section*

*(1 – 5) of the exercise rehabilitation programme outlined below. In addition, stretching exercises may be given as appropriate. You should aim to do your exercises twice daily.*

**1) LORDOSIS MINIMISING POSTURAL EXERCISES**

*progress from a. to e. as appropriate*

a. Posterior pelvic tilt/lordosis flattening exercises in standing against wall, knees slightly

flexed

b. Posterior pelvic tilt/lordosis flattening exercises in standing against wall with knees

extended

c. Posterior pelvic tilt/lordosis flattening exercises in standing without wall

d. Posterior pelvic tilt/lordosis flattening exercises while marching on spot

e. Posterior pelvic tilt/lordosis flattening exercises during normal walking

**2) SPINAL FLEXION EXERCISES**

*include one of the following exercises*

a. Knee to chest curls in crook lying

b. Lumbar flexion in sitting – reaching fingertips to floor

c. Lumbar flexion exercises in standing - reaching fingertips to ankles

**3) ABDOMINAL MUSCLE STRENGTHENING EXERCISES**

*include one of the following exercises*

a. static transverse abdominus muscle static contraction in crook lying

b. alternate knee lifts in crook lying, maintaining neutral lumbar position

c. abdominal curls reaching finger tips to knees

**4) GLUTEAL/ TRUNK MUSCLE STRENGTHENING EXERCISES**

*include one of the following*

a. bridging, weightbearing through both feet

b. bridging, one leg crossed over the other, weightbearing through one foot only

c. bridging, extending alternate knees

**5) AEROBIC CONDITIONING EXERCISES**

*include one of the following exercises to tolerance, increasing by 1 minute*

*each week*

a. knee dip/ calf raise alternating exercise

b. walking

c. cycling

d. step-ups

**6) STRETCHES** *include if required*

a. hip flexor muscle stretches (in prone lying, side lying or standing)

b. calf muscles stretches (in standing or on step)

